## Abstract

**Background:** Early childhood is a key period for reducing the social inequalities that affect health. Some parenting support and home visitation programs have proven to be effective in assisting parents during this period. France's *Protection Maternelle et Infantile* (maternal and child welfare) services (PMIs) are at the heart of this primary prevention and may adapt their intervention to improve parenting support. In this manuscript, we describe the protocol of the PERL study, an intervention based on a home visiting program.

**Method and design:** The PERL study is a single-center, randomized, controlled interventional trial. The aim was to assess the impact of a preventive home visiting program on the development of young children and parent-baby interaction. Visits were made by PMI nurses to 64 randomly recruited families from the general population. All families who had a baby born after 37 weeks of pregnancy between September 2018 and December 2019, and who resided in the trial area were eligible. Participants were randomly allocated to the intervention group or the control group. The PMI nurses made 12 home visits in the first year, 6 in the second year, and 4 in the third and fourth years of the child's life. Primary and secondary outcomes were measured when the child was 4 and 24 months old. These measurements recorded (i) the child's developmental milestones, in particular, language and socio emotional skills, (ii) early interaction, maternal sensitivity, and attachment patterns, (iii) maternal psychopathology including depression.

**Discussion:** This study aims to assess the impact of home visits, made by specifically-trained and supervised nurses, on the child's development and parent-child interactions. Such interventions are complementary to other preventive programs addressing the impact of social inequalities on perinatal health. Placing nurses' professional skills at the center of this project may prove an effective and cost-saving intervention compared to existing programs. The study proposes a prevention model that is in keeping with the principle of reducing social inequalities in health by providing support from the earliest age through public service.

**Clinical Trial Registration:** The clinical trial number is NCT03506971, registered on April 24, 2018.

## Background

### Early Childhood

Public health policies encourage primary prevention. Early childhood is a key period for reducing health social inequalities, and a priority in French health policy (1). Parenting support is promoted because it is recognized as a potentially valuable action (2–7).

In the first 3 years of life, a child goes through a period of dynamic growth (communication, interaction, psychomotor, and emotional development, etc.), which is considered to be the most important developmental stage in their life (8). It has been proven that the quality of a child's development during this early period is correlated with social interaction and mental health throughout life (9).

### Early Intervention

Literature shows the positive effects of early intervention in infant mental health prevention (10, 11). Early intervention is defined as the treatment of children under the age of 2 years and their parents in a therapeutic setting, to foster early attachment bonds (12).

Focusing on prevention, interventions to prevent and promote infant mental health issues are mostly intended for families deemed to be “at risk” (13–16). They can focus on the parent, child, and parent-child interaction or family, social services, and community support. These interventions have a positive effect on child development, parenting skills, parent self-esteem, parent-child attachment, bonding, and access to support and welfare services.

### Home Visits

Early prevention programs that include Home Visits (HV) incorporate the family environment into care, i.e., an environment that is familiar and often more reassuring for families (17). These programs are expected to reduce the impact of social stress factors on families, and promote parenting skills, especially in vulnerable families. Home-based parent-baby intervention generates changes, for example, parents are often more independent, with improved parenting skills, mothers are less depressed, attachment is more secure, and there are fewer behavioral disorders (16).

HV has been proven to be effective, with positive results in terms of the child and mother's mental health, early bonding, and more globally, on child development (18–20). The results of the STEEP (Steps Toward Effective, Enjoyable Parenting) program show that, at 24 months, parents who benefited from HVs had a better understanding of their baby's crying patterns, feel more positive about themselves, are less depressed, focus more keenly on pleasurable activities, and shared well-being involving the baby (21).

Moreover, a combination of weekly HVs with professional supervision has a substantial impact, including greater maternal empathy, reduction in avoidance or resistant behavior in young children, and the positive introduction of parent-child attachment bonds (22).

### HV and Prevention in France

The French government recently set up the First 1,000 days of life commission (23), highlighting the importance of this stage in a baby's development and the support needed by families during this crucial period.

In France, studies have tested the effectiveness of HVs in the perinatal period (24–26) (Table 1). We built the PERL study protocol drawing upon the strengths of these studies with the specific aim of proposing a protocol that can be blended into current practices (section Methods and Analysis).

**Table 1 T1:** French research on HVs.

	**CAPEDP (26)**	**INTERREG (27–29)**	**PANJO (30, 31)**
Characteristics	HV	HV	HV
Objective	Assess the impact of HVs carried out by attachment-trained psychologists on postnatal depression, the quality of the home environment and the psychological disorders	Evaluate the impact of HV carried out by a psychologist on language delays and child development	Adapt and experiment in PMI services a promotion system health, attachment support and evaluate the parent-child attachment
Population concerned	young mothers (<26 years) with vulnerability criteria	General population across 3 counties of the Lunevillois area	Primiparous and isolated mothers
Duration of study	24 months	24 months	6 months (up to 12 months if necessary)
Number of HVs	44	23	6 (until 12)
Professional	Psychologist	Psychologist	PMI nurses
Characteristics of the setting	- Training on the attachment theory, community psychology, developmental guidance, use of home video - Weekly individual supervision	−2 supervisions per month	- Training at the attachment theory - Supervision (frequency not specified)
Characteristics of the content of the HVs	- Observation - Discussion with parents and child Use of specific tools: video, playing cards to enable verbalization - Intervention mainly focused on the quality of the parent-child attachment and process related to attachment	- Observation - Interaction with parents and parent-child interaction through play - The content was mainly non-directive and not “interventional” - Based on psychoanalytic theoretical basis	- Observation - Discussion with parents and child - Use of attachment intervention guide and specific tools: video, playing cards to enable verbalization - Intervention mainly focused on the quality of the parent-child attachment and process related to attachment
Results	Does not show any significant difference in postpartum depression at 3 months vulnerable mothers - Highlights a better use of the care network (mainly PMI) - Highlights a better buy in from families when in their social environment	- Reduction in language delay - Significantly better psychomotor development at 2 years. - Significantly reduction in the number of children referred for psychological and/or speech therapy in the participant cohort at 4 years old	- The quantitative results of this research have not yet been published - The program was seen by the professionals of PMI as beneficial for their practice, even if the program supported interventions of the PMI among families and promoted a better understanding of the missions of PMI

### What Is the PMI Service?

The PMI is the maternal and child welfare service of France. It is a free public service for all French families, run by early childhood professionals. One of the main tasks of the PMI is to make primary prevention universal through HVs. PMI nurse interventions are based on guidance, providing advice on nutrition, development, the sleep/wake cycle of the baby, and so forth.

A previous national study has highlighted that PMI HVs are rarely part of a structured program (so typically lack stated objectives, guidelines, framework, training, etc.) (32, 33).

### The Content of HVs in Studies

HVs are centered on child development, the strengthening of parenting skills, the quality of early parent-child interactions (34), and the impact of the health professional on these aspects, according to the model of Fraiberg (12).

One of the main support criteria is based on the quality of the relationship between the support-giver and the parent (35): “most situations are first and foremost in need of a human/humanist touch, and this is very often all it requires” (36). Through regular HVs, the professional bolsters the security of the family bond by offering a constant and reassuring attachment, becoming an attachment figure for the parent (37). A PMI nurse may be used as a “resilience mentor” (38) by creating a temporary safe base (39, 40). This allows the parents to experiment, both mentally and physically, with a secure relationship which they can then transfer into the relationship with their child.

Several English-language studies (41, 42) have found that an adult who experienced an adverse childhood event needs to forge a rewarding relationship with the therapist. These parents are present in the general population. The professional's confidence in the ability of both parent and child can boost not only their confidence in themselves but also in the support available to them (43).

According to the literature, three key HV concepts are important:

(1) Parenting support: the professional listens actively and attentively, facilitating the emergence of imaginary and narcissistic representations relating to the baby. This parental support would enable a secure attachment to be formed among the children. Five components make up the relationship with the caregiver, and increase parents' receptiveness toward their baby (12, 14, 44, 45):

- Emotional support for parents;- Assistance with resources and requirements;- Developmental guidance for encouraging and strengthening the quality of attachment between parents and baby, helping parents to understand the “language” of their child and devising new educational methods;- Infant-parent psychotherapy: the exploration of the thoughts and feelings which are awakened in the baby's presence;- Use of the “echo function” (46) to speak for the children who cannot speak and where the parents are too overwhelmed by their emotions.

It is important to strengthen parenting skills (47). It is important to “take care of the person who takes care of others” (48). Listening to the difficulties encountered by the parents, and their need for reassurance, allows the parents to rekindle their ability to protect and support the baby (12, 48, 49).

(2) Observing the baby: Observation is considered an effective therapeutic action (50). Observing babies and their progress enables parents to identify with the “observing function” and so improve their child's development. According to Fraiberg (12), we give attentive and empathic responses to the parents, which can then be applied by the parents to the relationship with their child, paying particular attention to the emotions and behavior associated with past experiences. Active, attentive watching during observation can provide reassurance and strengthen the parent-child relationship (51, 52).

(3) Encouraging parent-baby interaction: as attachment theory has shown (39), from birth babies are social beings for whom interactive exchanges with a caregiver represent a primary need. Health professionals must therefore be interested in gradually building attachment bonds, and invite the parents to form a relationship with the baby through care, play, or active observation.

Play is a fundamental mediator in this interaction, allowing exchanges through different methods (visual, vocal, physical) and engaging each of the partners in a relationship that brings mutual pleasure. It represents a real “emotional bridge between parent and child,” the parent helping the child to develop through play (53, 54). Play may also be therapeutic in its own right (55, 56). Some therapeutic strategies focus almost exclusively on parent/child play to facilitate development and introduce a secure parent/child relationship (57).

With PERL, we propose follow-up interactions that encourage the child's development, strengthen the parents' ability to cope with their little one, and highlight the development and importance of early parent-child relationships (12, 44).

In the PERL study, HVs are included in a structured program, with guidelines, working methods, and professional training.

### Objectives of the PERL Study

The main objectives are to assess the effects of regular preventive HVs performed by PMI nurses on the prevalence of developmental and language delays in children, by comparing intervention and control groups.

The secondary objective is to longitudinally analyze the impact of the intervention for each family over the child's fourth to 24th months. The impact will be studied through the evolution of the child's development, looking at therapeutic alliance, parental feelings about the intervention and maternal mental health, quality of mother-child interactions, and experience of parenting.

PERL is an intervention system because a professional accompanies the family with tailored support. It is also a prevention system because this intervention begins before any disorder or diagnosis of delay. The goal in terms of mental health protection is to reduce the incidence of disorder by eliminating or reducing risk factors, and by intervening before symptoms develop. We propose with PERL a primary prevention program through intervention.

### Outline of the Trial and Hypotheses

The PERL action-research study is a single-center, randomized, controlled, interventional trial over a 4 year period that compares a group receiving regular preventive monitoring at home with a group that does not receive this intervention.

We expect a positive effect from the HVs performed by specifically-trained and supervised PMI nurses on:

- Children's development: we expect to observe for the intervention group at 24 months less developmental delay, less relational withdrawal, and fewer social and emotional difficulties. We also expect participants in the intervention group to have at 4 years a lower prevalence of language delay compared to the control group.- Parent-child interaction: we expect to find in the intervention group at 24 months greater reciprocity and continuity in interaction, better emotional relationship, and more maternal behavior, which facilitates exploration of the environment.- Experience of parenting: we expect in the intervention group at 24 months to observe more descriptors and positive markers in the mother's speech- Maternal mental health: we expect to find in the intervention group at 24 months less depression and fewer psychiatric symptoms.- Attachment: we expect to find in the intervention group at 24 months more secure attachment.- Maternal sensitivity: we expect to observe in the intervention group at 24 months a more “sensitive” mother profile in comparison with the control group.

## Methods and Analysis

In our opinion, the research presented in Table 1 has several limitations in terms of:

- the selection of a specific population (26, 35, 36);- reliance on professionals who are not usually involved in this preventive care (26, 32–34);- having a follow-up of ≤ 24 months (26, 32–36);- being based only on very specific theories (26, 32–36).

For PERL, we drew on the strengths of previous studies (cited in Table 1), bypassing the limits and choosing to offer intervention:

- in the general population;- by relying on existing practices;- using an eclectic theoretical model;- over a longer period, until the child reaches 4 years old.

### Sample

#### Context of the Lunevillois Area

The study was located in a rural, semi-rural, and urban area of eastern France called “Lorraine,” and was named the PERL study: *Petite Enfance, Recherche-action en Lorraine* (*Early childhood, action-research in the Lorraine area*). The context of the Lunevillois area is described in Table 2.

**Table 2 T2:** Context of the Lunevillois area.

**On 31.12.2018**	**Lunévillois**	**France**
Employment rate 15–64	62.8%	63.9%
Unemployed persons 15–64	13.8%	13.6%
Inactive people 15–64	27.1%	26%
Persons who benefit from an income of Active Solidarity (RSA) (for 1,000 persons 15–64 years)	42.4%	40.6%
Density of general practitioners (for 10,000 persons)	10.5	9
Number of PMI's consultations	73%	83% (in Lorraine)
Children with social or justice support (minor placed, educator,…) for 1,000 children under 20 years	32%	26.7% (in Lorraine)
School enrolment 2–5 years	73.5%	73.7%

*Lunévillois area: 1,576 km^2^, 178 towns, 67 inhabitants per km^2^*.

#### Determination of Sample Size

A calculation of sample size was carried out with one case per one control, a power of 80%, an alpha risk of 5%, a global developmental delay (obtained with the BLR test) prevalence rate of 50% in the controls and 25% in the children on the program (based on INTERREG results). The result obtained is a sample of 58 people in the intervention group and 58 in the control group. Taking into account the potential loss of 10% of subjects over the course of this ongoing research, 64 subjects were originally recruited for the intervention group and 64 subjects in the control group.

#### Sample Characteristics

- Eligibility criteria

There were two eligibility criteria: (i) the child was to have been born between September 2018 and December 2019 in the general population; and (ii) all families had their main residence in the *Pays Lunévillois*, in Lorraine, France.

- Exclusion criteria

There were three exclusion criteria: (i) a child born prematurely, before 37 weeks of pregnancy; (ii) families that did not speak French; (iii) non-settled traveler families, temporary refugees, and families with no fixed abode.

Participants were not prohibited from taking part in other research projects during this trial.

- Randomization (Figure 1)1) Every month, the PMI service sent the coordinating psychologist (SB) a list of all pregnancies reported in the population residing in the recruitment area, in the seventh month of pregnancy (on average 60 births per month).2) SB then sent a letter to all of the families on the list, informing them that research was being conducted and that they were likely to be contacted and invited to participate. This letter informed the families that they had 2 weeks to refuse participation.3) Two weeks later, SB performed the randomization process (Zelen randomization with a double consent for the 2 groups) based on the updated list of reported pregnancies post-refusal and returns for wrong address after the first letter had been sent. The families were thus randomly assigned to either the “intervention” or the “control” group.4) SB then sent a second letter informing families that they have been randomly selected to take part in the PERL study and forwarded a brochure describing the terms of participation (purpose of the study, how to participate, a presentation of the relevant stakeholders) with a suggested date for an HV (the start of the 8th month of pregnancy).5) If no refusal was received from the families, SB performed the HV to outline the trial to them, and if they agree to take part in the study they were asked to sign consent forms.

**Figure 1 F1:**
[figure not shown]
Recruiting method of the PERL study.

This recruitment method was highly formalized to meet the needs of research. Families were randomized in accordance with Zelen randomization before consent was requested to prevent the families' preference for one or another group and to avoid disappointment at not being in the intervention bracket. However, all parents may benefit from the PERL study: control group parents still had two assessments of their child's development, which could be reassuring. As double-blind evaluation cannot be performed in the PERL study, to circumvent this limitation, analysis will be performed by a professional who does not know the attribution group.

#### Rate of Inclusion

The PMI nurses in the area have taken on the PERL system in addition to their normal workload. As a result, we have had to adapt the number of families followed by each nurse to match the resources allocated by the PMI service. The PMI nurses were able to take on up to four families each, with 16 PMI nurses taking part in total. The control group was recruited with the same number of participants each month in order to avoid any bias (seasonality, etc.) and so that SB could perform the evaluation HVs within the allotted time. When the expected number of families per month (1 per PMI nurse) was reached, recruitment then stopped for that month and resumed the following month. In practice we had to limit the number of study participants to 128 families to enable coordination and feasibility in the field.

The number of PMI nurses participating in the project changed over the months (from September 2018 to September 2019). There were 6 PMI nurses over the first 3 months, 9 the following 7 months, then 10 professionals from May 2019, and at least 16 from September 2019.

The maximum number of subjects recruited has therefore changed according to the number of professionals involved in the research, 16 professionals being the necessary number to recruit the entire population. Furthermore, for reasons outside the study, recruitment was interrupted for 4 months (January 2019 to April 2019).

If we had been able to involve the desired number of professionals at the start of the research, we would have reached our recruitment goals within 5 months.

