### Data Analysis

All the conditions of use of the tests will be checked before using them. A significant level is <0.05 for all tests.

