#### Comparative Analysis

The effects of the support will be assessed by comparison with the control group. The student's *t*-test will be used for the comparative analyses of the quantitative variables. The chi-squared (χ^2^*)* test will be used for the comparative analyses of the qualitative variables. We will also compare the basic characteristics of populations who refused to take part with those who agreed to be included in the study.

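### Intervention families share about 16 nurses, but the planned tests and the sample size treat all families as independent; if nurses differ, the 5% level and the 80% power are somewhat optimistic

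*Protocol article*

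**What the plan says.** All places are in the protocol article.

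- **Randomisation** (Sample Characteristics): the family is the unit allocated.
- **Delivery** (Rate of Inclusion): "The PMI nurses were able to take on up to four families each, with 16 PMI nurses taking part in total". The same section says that nurse numbers grew from 6 to at least 16 during recruitment. Evaluation in Both Groups refers to a nurse dedicated to each intervention family.
- **Controls** (Control Group): they receive no specific intervention, but may use ordinary PMI consultations.
- **Sample size** (Determination of Sample Size): the inputs are "one case per one control", 80% power, 5% alpha and a "prevalence rate of 50% in the controls and 25% in the children on the program". The section reports the outcome of that calculation as follows: "The result obtained is a sample of 58 people in the intervention group and 58 in the control group". Recruitment was then set at 64 per arm to cover an expected 10% loss. No ICC or design effect appears.
- **Analysis** (Comparative Analysis): Student's t-test "will be used for the comparative analyses of the quantitative variables", and the chi-squared test serves the qualitative ones. Data Analysis adds that the tests' conditions of use will be checked, and "A significant level is <0.05 for all tests".

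**The concern.** The design is partially nested: one arm is grouped by nurse and the other, as far as the trial's own intervention goes, is not. Both named tests assume that families are independent of one another.

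The article itself gives reasons to expect some correlation within a nurse. It presents the quality of the bond between parent and professional as a main ingredient of the support (The Content of HVs in Studies). Nurses joined at different times, and those joining later are described as being introduced to the trial through an interview with the coordinator (Working and Exchange Days). The dedicated nurse attends the 4- and 24-month evaluation visits in the intervention arm, and Table 3 lists psychologist and nurse as raters of the attachment Q-sort. Clinical and Research Implications plans to study how factors such as professional alliance shape the effects.

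If nurses do differ, the variance of the intervention-arm mean or proportion is larger than the tests assume. Confidence intervals are then too short and a test labelled 5% rejects more often than that. A single result near the 5% boundary could be read as firmer than it is, in a trial whose stated aim is to inform national roll-out.

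**Working it through.** **Inputs from the article.** Control rate 0.50, intervention rate 0.25, difference 0.25, alpha 0.05 (taken as two-sided, which reproduces the stated size), power 0.80, 58 evaluable and 64 recruited per arm, 16 nurses.

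**Input not in the article.** The ICC. I assume 0.02 to 0.20 and show the range.

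**Step 1: reproduce the stated size.** With mean rate 0.375, so 0.375 × 0.625 = 0.234375:

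n = [1.96 × √(2 × 0.234375) + 0.8416 × √(0.25 + 0.1875)]² / 0.25² = (1.3419 + 0.5567)² / 0.0625 = 57.7, so 58.

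This matches. Power at 58 per arm is 80.2%. The formula assumes independent families in both arms.

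**Step 2: cluster size.** 64/16 = 4 families per nurse as recruited; 58/16 = 3.6 as evaluable. I use both, with equal clusters.

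**Step 3: design effect, intervention arm only.** DE = 1 + (m − 1) × ICC. At m = 4 this is 1.06, 1.15, 1.30 and 1.60 for ICC 0.02, 0.05, 0.10 and 0.20.

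**Step 4: consequences with 58 per arm.**

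- True SE divided by assumed SE, equal variances: √[(1 + DE)/2].
- Type I error of the unadjusted test: 2 × [1 − Φ(1.96 × √(2/(1 + DE)))].
- True SE under the alternative: SE₁ = √[(0.25 + 0.1875 × DE)/58].
- Power, unadjusted test: Φ[(0.25 − 1.96 × √(0.234375 × 2/58))/SE₁].
- Power, nurse-adjusted test: Φ[(0.25 − 1.96 × √(0.234375 × (1 + DE)/58))/SE₁].

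Worked example, m = 4, ICC 0.10, DE = 1.30: SE₁ = √(0.49375/58) = 0.0923. The unadjusted null SE is 0.0899 and the adjusted one 0.0964. Unadjusted power = Φ[(0.25 − 0.1762)/0.0923] = 78.8%. Adjusted power = Φ[(0.25 − 0.1890)/0.0923] = 74.6%. Type I error = 2 × [1 − Φ(1.828)] = 6.8%.

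| ICC | SE ratio (m = 3.6; 4) | Type I error, unadjusted | Power, unadjusted | Power, nurse-adjusted |
|---|---|---|---|---|
| 0 | 1.000 | 5.0% | 80.2% | 80.2% |
| 0.02 | 1.013; 1.015 | 5.3%; 5.3% | 80.0%; 79.9% | 79.2%; 79.1% |
| 0.05 | 1.032; 1.037 | 5.8%; 5.9% | 79.6%; 79.5% | 77.7%; 77.4% |
| 0.10 | 1.064; 1.072 | 6.5%; 6.8% | 79.0%; 78.8% | 75.3%; 74.6% |
| 0.20 | 1.124; 1.140 | 8.1%; 8.6% | 77.9%; 77.6% | 70.6%; 69.3% |

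**Step 5: check by simulation.** With 16 nurses (10 with four families, 6 with three, total 58), at ICC 0.05, 0.10 and 0.20:

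- Unadjusted chi-squared, beta-binomial data, 200,000 runs: type I error 5.9%, 6.7%, 8.3%; power 79.1%, 78.7%, 77.5%.
- Student's t-test, normal data, 100,000 runs: type I error 5.7%, 6.5%, 8.3%.

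**Step 6: if nobody is lost.** With all 64 per arm evaluable and m = 4, nurse-adjusted power is 81.4% at ICC 0.05 and 78.8% at 0.10.

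The normal approximation ignores the degrees of freedom lost with only 16 nurses, so the adjusted power figures are slightly generous.

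**The case against.** **A reader might infer that the planned tests fail to deliver 80% power.** The table does not support that. The unadjusted chi-squared test loses under 3 points even at ICC 0.20; what it loses is control of the error rate. The 69% to 78% figures describe a corrected analysis.

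**A reader might also infer that every between-arm test exceeds 5%.** That does not follow either. Families are individually randomised, so if the programme changes nothing for any family and nurses do not affect the measurement, the nurse cannot create correlation that upsets the test. Inflation needs real nurse-to-nurse differences around a zero average effect, or nurse involvement in scoring. On scoring, Strengths and Limitations promises blinded analysis of the video-based tests, including the attachment Q-sort. The neonatal comparison of 10 families per arm in the first 30 days comes when visits have barely begun, and is not at issue.

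**The ICC is unknown.** True. At 0.02 the type I error is about 5.3%, and no passage supports any particular value.

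**Controls may not be unclustered.** Also true. Control families may use ordinary PMI care, and Strengths and Limitations says that most nurses in the area take part. Some controls may share those nurses, so a model that treats each control as its own cluster is an approximation.

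**The cluster structure is loose.** The number of nurses is given as 16 and as at least 16, four families is a ceiling, and a family may change nurse (Data Collection). More nurses would mean smaller clusters and a smaller effect.

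**The nurse variance will be poorly estimated.** By the ANOVA estimator with 15 and 42 degrees of freedom, it would be zero or negative in about 37% of trials at ICC 0.05 and 24% at 0.10. This argues for a small-sample method, not for leaving the nurse out.

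**An analysis plan may deal with this, and the conditions of use will be checked.** An analysis plan is not shown. The article, however, names the tests and the power outright, and its sentence on checking names neither nurse clustering nor a remedy. The admission that the small sample may show no significant difference concerns sample size, not nesting.

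**Conclusion.** The point holds conditionally. It is certain that the intervention arm is nested in nurses and that the named tests and the sample size ignore this. How much it matters depends on an ICC that the documents do not give. For ICC 0.05 to 0.20, with 58 evaluable families per arm and 3.6 to 4 per nurse, the planned tests run at about 6% to 8% instead of 5%. At 0.05 or below the effect is small, and it becomes material from about 0.10. The stated 80% is correct only for a zero nurse ICC; a valid analysis would have about 77-78%, 75% and 69-71% at ICC 0.05, 0.10 and 0.20. The change is worth making before the comparative analysis, but the point does not undermine the trial.

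**What to change.** 1. For post-intervention outcomes compared between arms, replace the plain t and chi-squared tests with a partially nested model: a nurse random effect in the intervention arm only, each control family as its own cluster, and small-sample degrees of freedom. Nurse-cluster-robust standard errors with a small-sample correction are an acceptable alternative. Analyse each family under its first assigned nurse, whatever changes follow.
2. Add a sensitivity analysis for control families followed by a participating PMI nurse. The article already plans to identify controls with traditional PMI follow-up at 4 and 24 months; the nurse's identity would need to be noted as well.
3. Report the estimated nurse ICC, state that the 80% power assumes it is zero, and give the range 77-78%, 75% and 69-71% for ICC 0.05, 0.10 and 0.20, marked as assumed values.

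The cost is analysis wording, slightly wider intervals and a slightly lower stated power. The nurse for each intervention family should be known from delivery. No extra families are needed, and recruitment has in any case closed.
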